# Effectiveness of a multimodal standard nursing program on health-related quality of life in Chinese mainland female patients with breast cancer: protocol for a single-blind cluster randomized controlled trial

**DOI:** 10.1186/s12885-016-2726-y

**Published:** 2016-08-31

**Keywords:** Breast cancer, Cluster randomized controlled trial, Health belief model, Health-related quality of life, Multimodal standard nursing program, Study protocol

## Abstract

**Background:**

Breast cancer and its treatment-related adverse effects are harmful to physical, psychological, and social functioning, leading to health-related quality of life (HRQoL) impairment in patients. Many programs have been used with this population for HRQoL improvement; however, few studies have considered the physical, psychological, and social health domains comprehensively, and few have constructed multimodal standard nursing interventions based on specific theories. The purpose of this trial is to examine the effect of a health belief model (HBM)-based multimodal standard nursing program (MSNP) on HRQoL in female patients with breast cancer.

**Methods:**

This is a two-arm single-blind cluster randomized controlled trial (cRCT) in clinical settings. Twelve tertiary hospitals will be randomly selected from the 24 tertiary hospitals in Xi’an, China, and allocated to the intervention arm and control arm using a computer-generated random numbers table. Inpatient female patients with breast cancer from each hospital will receive either MSNP plus routine nursing care immediately after recruitment (intervention arm), or only routine nursing care (control arm). The intervention will be conducted by trained nurses for 12 months. All recruited female patients with breast cancer, participating clinical staff, and trained data collectors from the 12 hospitals will be blind with respect to group allocation. Patients of the control arm will not be offered any information about the MSNP during the study period to prevent bias. The primary outcome is HRQoL measured through the Functional Assessment of Cancer Therapy-Breast version 4.0 at 12 months. Secondary outcomes include pain, fatigue, sleep, breast cancer-related lymphedema, and upper limb function, which are evaluated by a visual analogue scale, the circumference method, and the Constant-Murley Score.

**Discussion:**

This trial will provide important evidence on the effectiveness of multimodal nursing interventions delivered by nurses in clinical settings. Study findings will inform strategies for scaling up comprehensive standard intervention programs on health management in the population of female patients with breast cancer.

**Trial registration:**

Chictr.org.cn ChiCTR-IOR-16008253 (April 9, 2016)

## Background

Breast cancer is the most common malignant tumor in the female population. Global statistics in 2012 indicated that about 1.7 million new cases were diagnosed and 522,000 died from the disease [1, 2]. In China, as in most other countries, breast cancer is prevalent in women. According to a report in 2014, Chinese cases accounted for 12.2 % of all newly diagnosed breast cancer cases and 9.6 % of all deaths from breast cancer worldwide [3]. Over the course of illness and treatment, breast cancer patients experience many acute and chronic adverse effects. They also face unique challenges to health and well-being as a result of their cancer, its treatment, and comorbidities [4–7].

Health-related quality of life (HRQoL) is broadly conceptualized as individuals’ perceptions of their physical health, psychological health, social relationships, relationship to their environment, independence level, and personal beliefs [8]. With changing medical models, HRQoL has been regarded as a key index for evaluating global therapeutic effects and survival status in populations of patients with cancer [9]. Given negative influences of the illness and treatment, breast cancer patients experience pain, fatigue, negative psychological states, self-image alteration, body function limitations, self-esteem reduction, and risk of recurrence, which severely impact physical, psychological, and social functioning [10–17]. Breast cancer patients also have been shown to have poorer HRQoL in comparison with the general population, especially among patients under 50 years of age [18, 19].

To improve HRQoL for breast cancer patients, many programs have been used with this population, such as art therapy (e.g., music therapy, dance/movement therapy) [20–22], exercise interventions (e.g., physical exercise/activity, resistance exercise, aerobic exercise, yoga) [23–28], psychoeducational support (e.g., health education, psychosocial support, spiritual group therapy) [29–33], and multimodal programs (e.g., rehabilitation programs, physiotherapy programs, exercise programs) [34–37], with different effects on HRQoL. However, existing or potential health problems in physical, psychological, and social domains have not been considered comprehensively. Additionally, the previously mentioned programs fail to describe intervention parameters such as time, frequency, or strength in an explicit manner, leading to their unsuitability as standard nursing interventions. Moreover, few studies have constructed a multimodal standard nursing program (MSNP) for breast cancer patient populations [38].

### Theoretical framework

The MSNP is developed based on the Health Belief Model (HBM), which attempts to explain and predict health behaviors by focusing on the attitudes and beliefs of individuals. The HBM comprises four constructs: perceived susceptibility, perceived severity, perceived benefits, and perceived barriers. These concepts are proposed to account for people’s readiness to act [39]. Cues to action are thought to activate readiness and stimulate overt behavior. Self-efficacy or confidence promotes the performance of an action. Moreover, a person will take a health-related action if it is felt that a negative health condition can be avoided, there is a positive expectation about taking a recommended action, and a belief exists that a recommended health action can be taken successfully [40].

The HBM has been widely used in different populations [41–45]. However, it has rarely been employed as a theoretical guide in developing nursing intervention strategies in patients with breast cancer [46–48]. Based on the HBM, influencing factors can be explored from physical, psychological, and social viewpoints. Therefore, perceived susceptibility (e.g., risk of deterioration or recurrence), perceived severity (e.g., complications due to delayed treatment), perceived benefits (e.g., positive feedback following MSNP implementation), and perceived barriers (e.g., impediments to MSNP implementation) can be identified during the treatment and nursing process to aid in the development of the MSNP (Fig. 1).

**Fig. 1 Fig1:**
[figure not shown]
Conceptual framework for the multimodal standard nursing program (MSNP) development

### Aims and objectives

The aim of this trial is to evaluate the effectiveness of a MSNP for female patients with breast cancer in Xi’an, China. The primary objective is to test for effects of the MSNP on HRQoL enhancement. The secondary objectives are to assess improvements in pain, fatigue, sleep, breast cancer-related lymphedema (BCRL), and upper limb function.

Based on these objectives, the primary hypothesis is that breast cancer patients receiving MSNP will achieve better HRQoL than a control arm at 12 months. The secondary hypotheses are that patients receiving the intervention will have (i) improved HRQoL at 1, 3, and 6 months; (ii) lower pain scores and less BCRL occurrence; and (iii) improved fatigue, sleep, and upper limb function at 1, 3, 6, and 12 months.

## Methods

### Design

This is a two-arm single-blind cluster randomized controlled trial (cRCT) in clinical settings with female breast cancer patients.

### Participants

Participants are inpatients with breast cancer. Inclusion criteria are newly diagnosed with breast cancer, female, aged 18 years and older, preparing to receive radical mastectomy and other auxiliary treatments (e.g., chemotherapy, radiotherapy, endocrine therapy), and providing written informed consent. Patients with cognitive disorders, psychiatric disorders, other malignant tumors, active infection, or other severe potential infection will be excluded. Cognitive disorders and psychiatric disorders will be screened using DSM-V (Diagnostic and Statistical Manual of Mental Disorders, 5^th^ ed.) criteria [49]. Reasons for refusal to participate will be documented.

### Sample size and randomization

The sample size was calculated based on the FACT-Bv4.0 total score of similar intervention studies (two-arm trials with Chinese mainland female patients with breast cancer employing a 12-month follow-up period). According to an eligible study [50], 74 patients (37 in each arm) will be needed to detect a between-arm change of 6.74 in the FACT-Bv4.0 total score with a power of 80 % at a 5 % level of statistical significance. The sample size was increased to 90 patients (45 in each arm) to allow for a 20 % dropout rate. Assuming an intra-cluster correlation coefficient (ICC) of about 0.1 and 30 patients per cluster, the sample size adjusting for clustering is 12 clusters or 360 patients [51]. That is, a total of 12 tertiary hospitals will be required in the trial, with 6 hospitals in each arm and 30 patients per hospital on average.

The 12 tertiary hospitals will be randomly selected from the 24 tertiary hospitals in Xi’an district and allocated to the intervention and control arms using a computer-generated random numbers table. Selection and allocation of the 12 hospitals will be carried out independently by a member of the research team.

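### The dropout allowance multiplies by 1.2 instead of dividing by 0.8, and the 80% power takes no account of having only 12 hospitals of possibly unequal size

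*Protocol article*

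**What the plan says.** All figures are in the protocol article, Methods, Sample size and randomization.

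- Before clustering: "74 patients (37 in each arm) will be needed". This is taken from a cited study, for a 6.74-point difference between arms on the FACT-B total, at 80% power and the 5% level.
- Dropout: "The sample size was increased to 90 patients (45 in each arm) to allow for a" 20% dropout rate.
- Clustering: with an intra-cluster correlation (ICC) of about 0.1 and 30 patients per cluster, "the sample size adjusting for clustering is 12 clusters or 360 patients".
- Layout: the trial will run "with 6 hospitals in each arm and 30 patients per hospital on average".

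The section gives no SD and does not say whether the test is two-sided. Under Data management and analyses, the primary endpoint is analysed by a linear mixed model with baseline as covariate and random effects for cluster and patient.

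**The concern.** Two consecutive sentences do not fit together. If 74 patients must be analysed and 20% are lost, the number enrolled has to be 74 divided by 0.8. The printed 90 falls short of that, and the clustering step is built on it.

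The clustering step has its own weakness. It counts patients as if the only cost of randomising hospitals were the design effect. With 6 hospitals per arm, the between-arm comparison also pays for estimating the between-hospital variance from few units. If hospitals recruit unevenly, the equal-size design effect is too small.

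At stake is the power for the 12-month FACT-B total score, the primary outcome. Anyone interpreting a null result would take 80% at face value.

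**Working it through.** **Inputs.** From the article: difference 6.74; 37 per arm; 80% power; 5% level; 20% dropout; ICC 0.1; 30 per hospital; 12 hospitals. Assumed: two-sided test; SD back-calculated from 37 per arm; coefficient of variation (CV) of hospital size.

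**1. Reproducing the plan.**
- Dropout: 37 × 1.2 = 44.4, rounded up to 45 per arm = 90. Exact match.
- Design effect: 1 + (30 − 1) × 0.1 = 3.9.
- Clusters: 90 × 3.9 = 351; 351 / 30 = 11.7, rounded up to 12 = 360 patients. Exact match, with no term for unequal sizes or few clusters.

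**2. The dropout step.**
- 90 × 0.8 = 72 (36 per arm), below 74.
- 90 covers a dropout of only 1 − 74/90 = 17.8%.
- Correct inflation: 37 / 0.8 = 46.25, rounded up to 47 per arm = 94.

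**3. Does the slip undo the 12 hospitals?**
- In the plan's own order: 360 / 3.9 × 0.8 = 73.8 effective patients, against 74 needed.
- On the patients analysed: 360 × 0.8 = 288, or 24 per hospital. Design effect 1 + (24 − 1) × 0.1 = 3.3. Requirement 74 × 3.3 / 24 = 10.2 hospitals, so 11, or 12 in equal arms.

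By large-sample theory with equal sizes, 12 hospitals are therefore enough.

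**4. Implied SD.** From 37 per arm at 80% power, the standardised difference is (1.96 + 0.84) × √(2/37) = 0.651, so SD = 10.35. With a t-test it is 0.660, so SD = 10.2.

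**5. Power for 12 hospitals and 288 completers.** Design effect with unequal sizes: 1 + ((CV² + 1) × 24 − 1) × 0.1. Effective n per arm: 144 / design effect. Noncentrality: standardised difference × √(effective n per arm / 2). Critical value: 1.96 for large samples; 2.228 for t on 12 − 2 = 10 degrees of freedom (df).

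For equal sizes: 144 / 3.3 = 43.6, and the noncentrality is 0.651 × √21.8 = 3.04 (3.08 with 0.660).

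| Hospital size CV | Design effect | Effective n per arm | Large-sample power | Power on 10 df | Detectable difference, 80% power, 10 df |
|---|---|---|---|---|---|
| 0 (equal) | 3.30 | 43.6 | 86.0–86.9% | 78.3–79.3% | 6.8–6.9 |
| 0.3 (assumed) | 3.52 | 41.0 | 83.8–84.8% | 75.7–76.8% | 7.0–7.1 |
| 0.5 (assumed) | 3.90 | 36.9 | 79.9–81.0% | 71.3–72.5% | 7.4–7.5 |

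The lower power and the larger detectable difference in each range go with SD 10.35; the other ends go with SD 10.2.

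**The case against.** The strongest reply is that nothing in the trial's size has to change. The dropout error is 3 to 4 patients before clustering, and step 3 shows that it does not by itself bring the design below 80%. That stands.

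Second, the power figures above are for an unadjusted comparison at 12 months, whereas the planned mixed model adjusts for baseline and uses all follow-up visits. A modest baseline correlation could lift power back over 80%. As an illustration, multiplying the variance by 1 − r² with an assumed r of 0.3 gives 82–83% for equal hospitals on 10 df. This stands as a caveat, but cannot be turned into a figure for this trial. The article gives no correlation, and the back-calculated SD may already refer to change scores, which would make the gain smaller. The plan's own calculation takes no credit for adjustment either.

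Third, the CV values are not in the article, and the ICC is only approximate. That also stands: the unequal-size rows are sensitivity scenarios and do not show an error in a printed figure.

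Two stronger readings are tempting.

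- **The trial needs 14 hospitals (420 patients).** This comes from 94 × 3.9 = 366.6, or 12.2 clusters, rounded up to equal arms. It applies the design effect for 30 analysed patients to a sample inflated for patients who will not be analysed. On completers the requirement is 10.2 hospitals by large-sample theory.
- **Power is only about 72% even with equal hospitals.** This applies 3.9 to hospitals with 24 completers, where equal sizes give 3.3. A design effect of 3.9 at 24 completers corresponds to a CV of 0.5, so the figure belongs only to that assumed scenario.

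**Conclusion.** The dropout step is wrong as written: 90 enrolled gives 72 completers where 74 are required. This is certain from the article's own numbers, and its practical effect is small.

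The weightier point is that the 80% power makes no allowance for few clusters or unequal hospital sizes. Without baseline adjustment, power is about 78–79% with equal hospitals, a shortfall of 1 to 2 percentage points. It is lower if recruitment is uneven: 76–77% at a CV of 0.3 and 71–73% at 0.5.

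These values rest on an ICC of exactly 0.1, a back-calculated SD of 10.2 to 10.35, two-sided testing, 20% loss in every scenario, and assumed CVs. A reader might infer that the trial is underpowered or too small. The article does not support that, because the planned adjustment may recover an amount of power that cannot be quantified from it. The point is a correction to a stated calculation and does not call for a larger trial.

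**What to change.** Keep 12 hospitals and 360 patients. Replace the dropout and clustering steps with one calculation on expected completers: 288 patients, 24 per hospital, design effect 3.3, t on 10 df. Changing 90 to 94 while leaving the rest would only create a new mismatch, since 94 × 3.9 = 366.6 exceeds 360.

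Restate the unadjusted power as about 78–79% with equal hospital sizes (86–87% by large-sample theory), with the sensitivity range for unequal sizes. Say that these figures use an SD of about 10.2 to 10.35 back-calculated from 37 per arm and assume a two-sided test, and that baseline adjustment may add power not counted here.

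The cost is a text correction and a slightly less favourable stated power. No patients or hospitals are added and recruitment is unchanged.

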### Procedure

Following random selection and allocation of the 12 tertiary hospitals, eligible female inpatients with breast cancer from each hospital will receive either MSNP plus routine nursing care immediately after recruitment (intervention arm), or only routine nursing care (control arm). The patients in both arms will provide demographic data and complete the pre-test of the FACT-Bv4.0, VAS, arm circumference, and CMS prior to the intervention. After the baseline measurement, four post-tests (i.e., FACT-Bv4.0, VAS, arm circumference, and CMS) at 1, 3, 6, and 12 months will be conducted. Items on the questionnaire will be asked of all patients and their answers will be recorded by trained data collectors. The flow chart of the cRCT procedure is depicted in Fig. 2.

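### No restriction beyond equal numbers is described for the draw of 12 known hospitals; stratified or constrained allocation would be a cheap improvement

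*Protocol article*

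**What the plan says.** The Sample size and randomization section gives the frame, "The 12 tertiary hospitals will be randomly selected from the 24 tertiary hospitals in Xi’an district", and the method of assignment, "allocated to the intervention and control arms using a computer-generated random numbers table". The numbers are fixed there too: "a total of 12 tertiary hospitals will be required in the trial, with 6 hospitals in each arm and 30 patients per hospital on average". In its abstract, the article describes the same selection ("Twelve tertiary hospitals will be randomly selected") and names the same source of random numbers.

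The Procedure section gives the order of events: "Following random selection and allocation of the 12 tertiary hospitals, eligible female inpatients with breast cancer from each hospital will receive" one of the two care packages. Selection and allocation of the hospitals therefore come before patient enrolment.

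No stratification, pairing, minimisation or constrained randomisation is described, and no hospital characteristic is listed. On the analysis side, the Data management and analyses section adjusts the primary model for the patient's baseline score and fits cluster and patient as random effects. It also plans a further model with pre-specified baseline covariates, which the article does not list.

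**The concern.** When all units are known before a single draw and there are only 12 of them, the investigator can choose among balanced allocations at almost no cost. A draw restricted only to six per arm gives that up. Characteristics such as hospital type or breast surgery volume (examples only) could fall unevenly, and six units per arm average out such differences poorly.

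The plan's own ICC of 0.1 makes this relevant, because most of the variance of a hospital mean then lies between hospitals. Balance and adjustment at hospital level act on that part; recruiting more patients per hospital does not. The timing also matters: a later statistical analysis plan can add covariates, but it cannot restrict a draw already made.

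**Working it through.** **Inputs from the article.** 12 hospitals, 6 per arm, 30 patients each, ICC 0.1, target difference 6.74, 37 per arm before inflation, power 80%, alpha 5% (taken as two-sided), dropout 20%. The SD is not stated.

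**The plan's own figure.** Design effect = 1 + (30 − 1) × 0.1 = 3.9. 90 × 3.9 = 351 patients; 351/30 = 11.7, rounded up to 12 clusters, or 360 patients. The stated size reproduces.

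**Share of variance between hospitals.** For a hospital mean with m patients the share is 0.1/(0.1 + 0.9/m). With m = 30 it is 0.1/0.13 = 77%. With m = 24 (30 × 0.8) it is 0.1/0.1375 = 73%.

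**Chance imbalance for one yes/no characteristic.** There are C(12,6) = 924 equally likely 6:6 allocations. If 6 hospitals hold the characteristic, the number of allocations putting x of them in the intervention arm is C(6,x) × C(6,6−x), which for x = 0 to 6 is 1, 36, 225, 400, 225, 36, 1.

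- 4:2 or worse: 2 × (1 + 36 + 225)/924 = 524/924 = 56.7%.
- 5:1 or worse: 2 × (1 + 36)/924 = 74/924 = 8.0%.

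Other prevalences, by the same count:

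| Hospitals holding it | Split | Probability |
|---|---|---|
| 5 of 12 | 4:1 or worse | 24.2% |
| 4 of 12 | 3:1 or worse | 54.5% |
| 4 of 12 | 4:0 | 6.1% |
| 3 of 12 | 3:0 | 18.2% |
| 2 of 12 | 2:0 | 45.5% |

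For a continuous characteristic the difference in arm means has SD sqrt(1/6 + 1/6) = 0.577 hospital SD. By normal approximation it exceeds 0.5 hospital SD with probability 39% and 1 hospital SD with probability 8%.

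**Possible size on the outcome scale (assumption).** 37 per arm imply, by the normal formula, SD = 6.74 × sqrt(37/2)/(1.960 + 0.842) ≈ 10.35. The between-hospital SD is then sqrt(0.1) × 10.35 = 3.27. A characteristic held by half the hospitals that explains a share R of between-hospital variance separates its two groups by 2 × 3.27 × sqrt(R) points. A 4:2 split passes one third of that to the arm difference, and a 5:1 split two thirds. For R from 25% to 100% this is 1.1 to 2.2 points at 4:2 and 2.2 to 4.4 points at 5:1, against the target of 6.74.

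**Power with and without restriction (assumptions).** Take SD 10.21 (6.74/10.21 = 0.66, which needs about 37 per arm by the t-test) and 24 completers per hospital, or 144 per arm. SE = SD × sqrt(2 × (1 + 23 × ICC)/144), and power comes from the noncentral t with 10 df, less one per hospital-level covariate. A lower ICC stands for the between-hospital variance that the balancing variables explain.

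- ICC 0.10: SE = 10.21 × sqrt(2 × 3.3/144) = 2.19, so 6.74/2.19 = 3.08.
- ICC 0.075: SE = 1.99, ratio 3.39.
- ICC 0.05: SE = 1.76, ratio 3.82.

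| ICC after adjustment | 10 df | 9 df (one covariate) | 8 df (two covariates) |
|---|---|---|---|
| 0.10 | 79.3% | 78.3% | 77.0% |
| 0.075 | 86.3% | 85.4% | 84.3% |
| 0.05 | 93.0% | 92.4% | 91.5% |

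The design as described is the 79.3% cell. A restricted and adjusted design belongs in the 9 df or 8 df column.

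**The case against.** **A table of random numbers does not exclude strata.** It names the source of randomness, and a journal article condenses a fuller protocol. This stands: the article supports only the statement that no restriction is described. A reader might infer that the trial has ruled out stratification, but the text does not say so.

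**Randomisation already deals with chance imbalance.** This also stands. The random cluster effect carries between-hospital variance into the standard error, so lack of stratification does not inflate the type I error. Adjusting for the baseline score removes the part of a hospital difference already visible at baseline, and the unlisted covariates may include hospital-level ones. A reader might infer that an uneven draw would confound and so invalidate the comparison. The analysis section does not support that; what remains is less precision, bias conditional on the allocation drawn, and a result that is harder to defend.

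**The 57% is a chosen case.** It holds for a characteristic held by exactly half the hospitals with 4:2 counted as an imbalance. The article lists no hospital characteristic, so nothing shows that any is held by half of them or predicts the FACT-B score.

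**The power gain is assumed.** No figure in the article says how much between-hospital variance any hospital variable explains. If the answer is none, two covariates lower power from 79.3% to 77.0%.

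What survives is that restriction suits this design, is cheap, and is possible only before the draw.

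**Conclusion.** The point holds as a recommended improvement, not as an error. The article fixes a 6:6 draw of hospitals known in advance and describes no restriction beyond equal numbers. For a characteristic held by 6 of 12 hospitals, the chance of a 4:2 or worse split is 57% and of 5:1 or worse 8%.

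A reader might go further and infer an even chance or worse of a clear imbalance in general. That is true only for a characteristic held by 6 or 4 of the 12, and only if a difference of two hospitals counts as clear. It fails for one held by 2, 3 or 5 hospitals (46%, 18%, 24%) and for a continuous one at 0.5 hospital SD (39%).

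The imbalance probabilities are exact counts, apart from the normal approximation for the continuous case. The outcome shifts and power figures rest on an SD that the article does not give, and the power gain also rests on an assumed fall in the ICC. They show a range, not a forecast.

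**What to change.** If allocation has not been drawn, do one of the following and state it in the protocol.

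- **Stratify the draw by one hospital characteristic**, such as hospital type or breast surgery volume. If it splits the 12 hospitals 6 and 6, drawing three of six in each stratum leaves 20 × 20 = 400 of the 924 allocations, and every one is balanced 3:3.
- **Use covariate-constrained randomisation.** List the 924 allocations, score each for balance on the chosen variable(s), keep a large candidate set (for example the best-balanced quarter, 924/4 = 231), and draw one at random. This also handles continuous variables and strata of odd size.

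In either case put the balancing variable(s) in the primary model. Prefer one strongly prognostic variable to several weak ones, because each uses one of the 10 between-cluster degrees of freedom and repays it only by explaining between-hospital variance.

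The cost is about an hour of programming, facts that the hospitals already hold, and one or two degrees of freedom; the trial stays at 12 hospitals and 360 patients. If a restriction was in fact used, the protocol should say which. If the draw has already been made without one, the remaining option is to pre-specify the hospital-level covariate(s) before unmasking.
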